## Methods

### Ethical Approval

This trial has been approved by the institutional review board at the University of Texas Health Science Center at San Antonio and the protocol review committee at the National Cancer Center Institute Mays Cancer Center at the University of Texas Health Science Center at San Antonio (2019-610H). All participants who meet the inclusion criteria will be eligible for participation. Any deviations from the protocol, breaches of confidentiality, and reportable adverse events will be reported to the institutional review board and Data Safety Monitoring Board at the Mays Cancer Center. The study is registered with ClinicalTrials.gov (trial number: NCT04207359).

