### Exercise Intervention

All participants will engage in 3 center-based exercise sessions each week for 12 weeks. Each session will last roughly 1 hour and include a 10-minute warm-up and a 50-minute stimulus phase. Exercise sessions will be held on nonconsecutive days to allow for adequate rest and recovery. The prescription will include 2 or 3 sets of 6 exercises, which will be performed at a 10-repetition maximum intensity (ie, participants will be able to perform only 8 to 12 repetitions per set), as per the American College of Sports Medicine’s guidelines for exercise testing and prescription [29] and the consensus statement on exercise guidelines for cancer survivors [30]. Each session will consist of the following exercises, which will be done in the following order: chest press, leg press, seated row, shoulder press, leg extension, and leg curl. The resistance load will be set at 70% of the measured or estimated 1-repetition maximum. If participants cannot perform an exercise with this resistance load, the load will be reduced to allow them to complete the prescribed repetitions for each set. Participants will complete 2 sets of each exercise in week 1. This will allow participants to familiarize themselves with the resistance load and will minimize the risk of injury for novice participants. Starting in week 2, participants will transition to performing 3 sets of each exercise. The load will be increased when a participant is able to perform 12 repetitions in 2 of 3 sets for an exercise. Participants’ heart rates will be monitored continuously during exercise sessions. Self-reported perceived exertion will also be recorded periodically during exercise sessions [31], and this information will be used to track the subjective experiences of participants and interpret adherence data.

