### Monitoring Adverse Events

Adverse events will be assessed during each interaction with a participant (ie, 3 times per week). Before and after each exercise session, participants will be asked about how they are feeling. If the answer is anything other than “feeling fine,” the participant will be queried about the date and time of the onset of an adverse event, self-perceived severity, and any self-administered treatments. Upon the conclusion of the intervention, each adverse event will be graded by medical professionals based on severity, the event’s relationship to the study intervention, the actions taken by the study personnel and participants, adverse event outcomes, whether the event was expected, and whether the event was serious. We will use the Common Terminology Criteria for Adverse Events version 5.0 [44] to grade the adverse events.

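### Medical classification of adverse events is set at the end of the intervention, which conflicts with the promise to report reportable events to the oversight boards

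*Protocol article*

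**What the plan says.** The Monitoring Adverse Events section of the protocol article separates collecting events from judging them.

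- **Collection.** Participants are asked how they feel before and after every exercise session, three times a week. If something is wrong, staff ask for the date and time of onset, "self-perceived severity, and any self-administered treatments".
- **Judgement.** The medical assessment has its own stated time: "Upon the conclusion of the intervention, each adverse event will be graded by medical professionals based on severity". The sentence goes on to list "the event’s relationship to the study intervention, the actions taken by the study personnel and participants", the outcome of the event, and "whether the event was expected, and whether the event was serious". Grading uses CTCAE version 5.0.

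The Ethical Approval section makes the reporting commitment: "reportable adverse events will be reported to the institutional review board and Data Safety Monitoring Board at the Mays Cancer Center". It gives no deadline and does not define which events are reportable.

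The Exercise Intervention section gives the length of the period: "All participants will engage in 3 center-based exercise sessions each week for 12 weeks".

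**The concern.** An event cannot be recognised as reportable until someone has judged whether it is serious, unexpected or related to the intervention. The article assigns those judgements to medical professionals and places them after the intervention is over. Staff who follow the text would collect events promptly and hold them unclassified, and the reporting promise in Ethical Approval would have no input until the participant had finished.

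What is at stake is the use of the reports. Both boards oversee participants who are still training and, in one arm, still taking creatine. A classification made after the last session can no longer inform oversight of that participant, and it comes late for others enrolled in the meantime.

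This is not a complaint that a condensed article leaves out a detail. The article states a time point, and that time point does not fit its own reporting commitment.

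**Working it through.** There is no planned figure to reproduce. The check is a comparison of sections, followed by simple arithmetic on the delay.

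**Step 1: what is known about an event, and when.**

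| Item | When, according to the article |
|---|---|
| Date and time of onset | At the contact, three times a week |
| Severity as the participant sees it | At the contact |
| Self-treatment | At the contact |
| CTCAE grade by a medical professional | Conclusion of the intervention |
| Relationship to the intervention | Conclusion of the intervention |
| Expectedness | Conclusion of the intervention |
| Seriousness | Conclusion of the intervention |

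The grading sentence applies to each event. It contains no exception for serious events, and no earlier classification step appears elsewhere in the article.

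**Step 2: what the reporting promise needs.** Ethical Approval limits reporting to adverse events that are reportable. The article does not define the term. I assume, as is usual, that it turns on some combination of seriousness, expectedness and relationship. All three stand in the deferred part of the table.

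**Step 3: length of the delay.** Take the intervention to mean the participant's own 12 weeks.

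- Total length: 12 weeks × 7 days = 84 days.
- Event at the very start: 84 − 0 = 84 days, or 12 weeks.
- Event at the end of week 1: 84 − 7 = 77 days, or 11 weeks.
- Event in the last week: 7 days or fewer.

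The Creatine Dosing Protocol section puts the loading phase in week 1, so 77 to 84 days is also the wait for an event during loading. If events were spread evenly over the 12 weeks, which is an assumption and not a figure from the article, the mean wait would be 84 ÷ 2 = 42 days. If the intervention means that of the whole trial, the waits are longer; the article does not say which is meant.

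**Step 4: whether another section supplies the missing step.**

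- *Creatine Dosing Protocol:* laboratory tests and electrocardiography follow the loading phase, with removal from creatine on renal thresholds. This is a kidney and heart check in one arm. It does not classify adverse events, and the exercise-only arm is not covered by it.
- *Table 1:* medical and medication history are taken at weeks 2, 5 and 9. No grading is attached to those visits.
- *Statistical Analysis:* withdrawal for safety reasons is foreseen, so someone makes safety judgements during the trial. The section does not say how these relate to adverse event classification.
- *Results:* as of October 2021, with 9 enrolled and enrollment still open, no unexpected events had been reported. Expectedness had therefore been considered for some participants, but these may have been only those who had finished.

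None of these changes the time stated in Monitoring Adverse Events.

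**The case against.** The strongest reply is that the grading sentence describes final coding of the event record and not the first recognition of a serious event. Its list includes actions taken and outcomes, which can only be completed in retrospect, and the same section says that events are assessed at every contact. The safety withdrawals, the post-loading checks and the October 2021 statement fit that reading, since they suggest that someone exercises judgement during the trial. A journal article may also leave reporting deadlines and expedited routes to the full protocol or a monitoring plan, and their absence here is no fault.

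Much of this stands. It limits how far the point can go, and three stronger readings that a reader might infer are not supported:

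- **That reporting cannot work in time, or that the boards cannot be told.** With no deadline in the article and a possible expedited route elsewhere, this goes beyond the text.
- **That nothing but the participant's own severity rating is recorded meanwhile.** Onset and self-treatment are recorded too, and the creatine arm has its own laboratory and electrocardiographic check.
- **That late grading is biased by knowledge of the arm.** The Allocation section says that the principal investigator and participants are unblinded and that the outcome assessor and statistician are blinded. It does not say whether the graders know the arm.

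The reply does not remove the conflict. If the sentence is meant as final coding, it should say so. As written it puts seriousness, expectedness and relationship at the end, together with items that do belong there. If in-course classification is already practised, the text misdescribes it and still needs correcting.

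**Conclusion.** The point holds as a conflict between two sections. Monitoring Adverse Events defers, for every event, the judgements on which the commitment in Ethical Approval depends. Taken literally, classification waits about 11 to 12 weeks for an event in week 1 and progressively less for later events, down to a few days in the final week. The rule covers both arms and all 30 planned participants, though the delay matters most for early events.

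This rests on three assumptions: that the intervention means each participant's own 12 weeks, that reportability depends on seriousness, expectedness or relationship, and that no other governing document sets an earlier step. If the last is wrong, practice may be sound and only the wording is at fault. The change should be made in either case, because it is inexpensive and bears on participant safety. It does not affect the efficacy analysis.

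**What to change.** Amend Monitoring Adverse Events to say that:

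1. a clinician judges CTCAE grade, seriousness, expectedness and relationship when the event is reported;
2. events that meet the reporting criteria go to the review board and the Data Safety Monitoring Board on those boards' own timelines;
3. the review at the end of the intervention remains, as a final reconciliation of actions taken and outcomes.

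If an expedited route already exists in the full protocol or a monitoring plan, one sentence referring to it, and stating that the end-of-intervention grading does not delay reporting, would reconcile the two sections.

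The cost is small but not nil. The judgements are the same, but the medical professionals must be available throughout the 12 weeks instead of once at the end. No new assessments or visits are needed.

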### Data Management

Each participant will be assigned a unique study code. Data will be saved and stored by using the REDCap electronic data management system. Surveys will be completed electronically and linked to the participants’ electronic data files to limit the incidence of transcription errors. Patients’ charts will be kept inside a locked cabinet that is located inside the clinical research space, which is directed by [name].

### Statistical Analysis

The proposed analysis of 30 participants is based on a feasibility assessment [45]. Based on a preponderance of published feasibility and pilot studies, a minimum sample size of 15 participants per group was chosen to complete the study and estimate parameters for future studies [46,47].

Data on recruitment, adherence, and attrition rates will also be collected. Participants that withdraw from the study or are withdrawn for safety reasons will not be replaced.

Statistical analyses will be performed by using IBM SPSS 19.0 software (IBM Corporation). Descriptive statistics will be used to summarize the data. The primary analysis will be an intent-to-treat analysis, which will be conducted by using a 2-sided, stratified log-rank test. Cox proportional hazard regression models will be used to estimate hazard ratios with 95% CIs to quantify the effect of the intervention after adjusting for stratification, age, and BMI. We will also conduct secondary analyses for nonadherence, the rate of perceived exertion, and the number of exercise sessions completed. Pearson product moment correlation analyses will be used to measure associations among biomarkers of body composition, physical function, and quality of life measures. A *P* value of <.05 will be considered statistically significant, and all statistical tests will be 2-tailed. The results of our study will be used to calculate power and determine sample sizes for future research in this field.

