### Study Objectives

The primary objective is to determine the effects of creatine supplementation, in combination with exercise, on modulating strength, body composition, and physical function in breast cancer survivors by comparing these effects to those of exercise alone. The primary hypothesis is that creatine supplementation will result in significantly greater gains in strength and physical function and improved body composition in breast cancer survivors compared to those resulting from exercise alone.

The secondary objectives are to determine if supplemental creatine can be used to increase intramuscular storages of creatine, alter energy storage, and improve quality of life. The hypothesis for these objectives is that creatine supplementation will significantly increase intramuscular concentrations of creatine and ATP in the vastus lateralis when compared to exercise-only controls. We also hypothesize that the creatine group will have significantly greater muscle cross-sectional areas and significantly lower levels of intramuscular fat compared to those of the exercise-only controls. Finally, we hypothesize that both groups will have a significantly better quality of life following the 12-week program.

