### Allocation

Patients who are eligible to participate in the study will be allocated to either the creatine and exercise group or the exercise alone control group (1:1). Randomization will be performed through the study’s REDCap (Research Electronic Data Capture; Vanderbilt University) database. We will use randomized blocks to conceal the group allocation results from the patients, recruitment staff, and assessment staff, and concealment will be maintained until the patients complete the baseline assessments. The research pharmacy at the Mays Cancer Center will conceal the randomization and will direct the research team to assign study participants to specific groups. A sample of 15 breast cancer survivors will be enrolled in each group with the goal of having 12 completers in each group. Due to the nature of the study, the principal investigator and study participants will not be blinded. However, to alleviate any issues with assessment fidelity, the research assistant who will be performing the outcome assessments will not be aware of the groups to which participants are randomized. Further, the statistician who will be supporting the analyses in the study will be blinded as well.

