### Capturing and Monitoring Adherence

Adherence to creatine supplementation will be assessed by measuring the quantity of creatine that is left in the returned bottles, as described in the *Creatine Dosing Protocol* section. Individuals will not be withdrawn from the study for noncompliance with the creatine dosing regimen. The dosing quantity (number of scoops) and the dosing time will be documented in a dosing diary. Each exercise session will be documented, and information regarding session duration time as well as exercise mode and intensity during each training session will be documented. Participants will be encouraged to adhere to the protocol to the best of their ability. Participants will be withdrawn if more than 33% (12/36) of exercise sessions are missed.

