## Discussion

Our project will determine if creatine—a naturally occurring substance in the body—that is consumed as a supplement can be used to improve the adaptation of exercise training and accelerate the gain of muscle mass, strength, and lean body mass. Individuals with cancer are exposed to a variety of factors that impact their ability to live active lifestyles. Some of these factors are tumor related [48], while others are related to cancer treatment [49]. The loss of muscle mass and function greatly impacts a breast cancer survivor’s quality of life [50]. The prevalence of muscle loss in individuals with cancer can range from 11% to 74% [51-56]. Exercise has been shown to combat this decline in muscle mass [56]. Exercise programs are capable of attenuating many of the deleterious effects of muscle loss [56]. Commercially available agents, such as creatine, have the potential to accelerate exercise adaptations and increase muscle mass, strength, and lean body mass [57,58].

Only 4 studies have been published to date on the effects of creatine supplementation in cancer survivors [22-25], and only 1 of the 4 studies involves creatine dosing in combination with an exercise program. In the combination study, which was conducted by Lønbro et al [22] in 2013, a total of 30 patients with head and neck cancer who were treated with radiotherapy were supplemented with 5 g of creatine per day. The investigators reported greater improvements in lean body mass for creatine-supplemented participants compared to those reported for participants who took placebos [22]. A limitation to the study by Lønbro and colleages [22] was that they did not use the suggested dosing regimen (20 g of creatine per day) at the start of the study to load intramuscular creatine concentrations. Research has demonstrated that this loading protocol can result in increased intramuscular creatine stores (ie, a 10% to 40% increase in muscular creatine and phosphocreatine stores). Using a lower dose will result in a gradual increase. Our study will be the first to investigate the effects of creatine supplementation in combination with exercise by using the recommended dosing protocol.

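### A size justified only for feasibility, with no allowance for loss in its stated minimum of 15 per group, is paired with efficacy conclusions it can reliably support only if the effect is large

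*Protocol article*

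**What the plan says.** On size, the Statistical Analysis section states: "The proposed analysis of 30 participants is based on a feasibility assessment". It then cites precedent from published feasibility and pilot studies and says that "a minimum sample size of 15 participants per group was chosen to complete the study and estimate parameters for future studies". It gives no effect size, SD, power or dropout rate. Power is left to later work: "The results of our study will be used to calculate power and determine sample sizes for future research in this field".

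On numbers, the Allocation section states: "A sample of 15 breast cancer survivors will be enrolled in each group with the goal of having 12 completers in each group". The Statistical Analysis section adds: "Participants that withdraw from the study or are withdrawn for safety reasons will not be replaced". Under Capturing and Monitoring Adherence there is also a withdrawal rule set by the protocol: "Participants will be withdrawn if more than 33% (12/36) of exercise sessions are missed".

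On purpose, the Study Objectives section sets a comparative efficacy objective. Its primary hypothesis is that "creatine supplementation will result in significantly greater gains in strength and physical function and improved body composition" compared with exercise alone. The Statistical Analysis section sets two-sided P<.05 as the significance rule. The Discussion opens with "Our project will determine if creatine", taken as a supplement, improves adaptation to training. Neither the Abstract nor the Study Objectives section contains a feasibility objective. Recruitment, adherence and attrition appear only as data that will also be collected.

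**The concern.** Two things do not fit together.

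First, 15 per group is called a minimum, yet enrolment is exactly 15, losses are foreseen and nobody is replaced. Outcomes are assessed only at baseline and at the end of the study (Outcome Assessments). A participant who withdraws and is not assessed at the end therefore contributes no final outcome.

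Second, the size is defended for one purpose and the inference is promised for another. A pilot of 30 is legitimate. It does not follow that a test at P<.05 on 30 participants, or 24, will settle whether creatine adds to exercise. A non-significant result could be taken as evidence of no benefit when the interval still includes moderate or large benefit. A significant result will on average overstate the effect when power is low. That matters because supplying parameters for later trials is the reason given for this size.

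**Working it through.** **The plan's own figure.** There is no power calculation to reproduce. The only arithmetic available is the allowance for loss: 12/15 = 0.80, an implied loss of 20%, and 12/(1 − 0.20) = 15. So 15 is what is needed to finish with 12. To finish with 15 after the same loss, enrolment would have to be 15/0.80 = 18.75, or 19 per group. This shows only that the two sections use 15 in different senses. It is not a proposal to enrol more.

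**Inputs.** From the article: n = 15 (randomised) and n = 12 (completer goal) per group, 1:1 allocation, two-sided alpha 0.05. Assumed, because the article does not give them: a continuous outcome compared by a two-sample t-test, 80% power as a benchmark, the true effect, and the baseline–follow-up correlation r. SD means the SD of the outcome being compared.

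**Precision, unadjusted.** Half-width of the 95% CI = t(0.975, 2n − 2) × √(2/n).
- n = 15: 2.048 × √(2/15) = 2.048 × 0.365 = 0.748 SD
- n = 12: 2.074 × √(2/12) = 2.074 × 0.408 = 0.847 SD

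**Difference detectable with 80% power, unadjusted.** The normal approximation is (1.960 + 0.842) × √(2/n), which gives 1.02 SD at 15 and 1.14 SD at 12. The noncentral t gives 1.06 SD at 15 and 1.20 SD at 12.

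**With baseline adjustment.** Multiply by √(1 − r²), which is 0.866 for r = 0.5 and 0.600 for r = 0.8.
- n = 15: 1.060 × 0.866 = 0.92 SD; 1.060 × 0.600 = 0.64 SD
- n = 12: 1.197 × 0.866 = 1.04 SD; 1.197 × 0.600 = 0.72 SD

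**Power over a range of assumed true effects (t-test).**

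| True difference (assumed) | 15 per group | 12 per group |
|---|---|---|
| 0.3 SD | 12% | 11% |
| 0.5 SD | 26% | 22% |
| 0.8 SD | 56% | 47% |
| 1.0 SD | 75% | 65% |
| 1.2 SD | 89% | 80% |

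With baseline adjustment at r = 0.5 to 0.8, power at 0.5 SD is 33% to 60% with 15 per group and 27% to 50% with 12.

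**The test the plan names.** The primary analysis is given as a stratified log-rank test, which the figures above do not describe. A rough bound, ignoring stratification, is that the hazard ratio detectable with 80% power = exp[(1.960 + 0.842)/√(events/4)]. If every participant had an event, this is exp(2.802/√7.5) = 2.8 with 30 events and exp(2.802/√6) = 3.1 with 24. That test also needs a large effect.

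**The case against.** The best defence is that the article is candid: it calls the size feasibility-based, claims no power, plans some 95% CIs and hedges in the Abstract's conclusions. A hypothesis is not a promised finding. This stands as far as it goes, and the small size is not itself the fault. It does not remove the mismatch, because the objectives, the significance rule and the Discussion are about efficacy.

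Several stronger readings are tempting but unsupported:

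- *The stated minimum will certainly not be reached in any outcome analysis.* The primary analysis is intent-to-treat on 30 participants, and the phrase about completing the study may simply mean carrying it out. Participants who do not comply with creatine are not withdrawn, and those taken off creatine because of laboratory results continue the exercise. Whether withdrawn participants are assessed at the end is not stated, and the full protocol may cover it. What stands is that the two sections need reconciling.
- *Any significant result must be exaggerated.* That depends on the true effect, which is unknown. If the true difference exceeds the significance threshold, a significant estimate can fall below the truth. The 0.85 SD threshold is also specific to an unadjusted comparison at 12 per group. With adjustment at r = 0.5 to 0.8 and one degree of freedom fewer, it is about 0.74 to 0.51 SD.
- *This size cannot show efficacy at all.* It can if the effect is large.
- *The next trial will be sized on the observed effect and so be too small.* The article says results will inform power and sample size. It does not say which parameter will be used, and variance or attrition would serve equally well. Nor does it say that a null result will be read as no effect.

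**Conclusion.** The point holds as a mismatch between justification and claim, and it should be corrected. The stated minimum of 15 per group has no allowance for loss unless withdrawn participants are still assessed. Reliable efficacy conclusions would need a true difference of roughly 1.1 to 1.2 SD unadjusted, or about 0.6 to 1.0 SD with baseline adjustment. A null result would leave an unadjusted interval of about ±0.75 to ±0.85 SD around the estimate, too wide to exclude a moderate benefit unless the estimate fell well on the unfavourable side.

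These figures assume a continuous outcome, a two-group comparison at two-sided 0.05 and, for the adjusted range, a correlation of 0.5 to 0.8. They describe the size of the trial and not the log-rank analysis that the plan names. Because no effect size is stated, no single power figure can be attributed to the plan.

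**What to change.** Keep 30 participants and change the wording in four places.

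1. Reconcile Allocation with Statistical Analysis. State 15 randomised per group and about 12 expected with outcomes, say whether withdrawn participants are still assessed at the end of the study, and give the resulting precision (95% CI half-width about 0.85 SD at 12 per group and 0.75 SD at 15, unadjusted).
2. In Statistical Analysis, report between-group differences in the primary outcomes as estimates with 95% CIs, labelled exploratory, and state that neither efficacy nor lack of effect will be concluded from P<.05.
3. Reword the primary hypothesis in Study Objectives and the opening of the Discussion to match.
4. State that future trials will be sized on a prespecified meaningful difference and an upper confidence limit for the SD, not on the observed effect. As an illustration, with 12 per group (22 degrees of freedom) the one-sided 80% upper limit is 1.16 times the estimated SD. The confidence level is a matter of convention.

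This needs no extra participants and no change to the interventions. The downside is a less ambitious stated conclusion.

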**Methods:**

We aim to test our hypothesis by conducting an open-label randomized controlled trial of 30 breast cancer survivors who have completed chemotherapy within 6 months of enrollment. Eligible participants will be equally randomized (1:1) to either a creatine and exercise group or an exercise-only group for this 12-week intervention. Individuals who are randomized to receive creatine will be initially dosed at 20 g per day for 7 days to boost the availability of creatine systemically. Thereafter, the dose will be reduced to 5 g per day for maintenance throughout the duration of the 12-week protocol. All participants will engage in 3 center-based exercise sessions, which will involve completing 3 sets of 8 to 12 repetitions on chest press, leg press, seated row, shoulder press, leg extension, and leg curl machines. The primary outcomes will include changes in strength, body composition, and physical function in breast cancer survivors. The secondary outcomes will be intramuscular concentrations of creatine and adenosine triphosphate in the vastus lateralis, midthigh cross-sectional area, and quality of life.

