#### Outcome Assessments

Assessments will be performed at baseline and at the end of the study (Table 2).

**Table 2 table2:** Study assessments and methods.

Assessment	Method
Renal function testing, metabolic panels, and lipid and complete blood count tests	Lab test
Muscle strength (power and torque)	Dynamometry
Muscle strength	1-repetition maximum and 10-repetition maximum training
Body composition and bone density	Dual x-ray absorptiometry
Muscle cross-sectional area	Magnetic resonance imaging
Muscle creatine, phosphocreatine, and adenosine triphosphate	Magnetic resonance spectroscopy
Physical function	6-minute walk test
Quality of life	European Organization for Research and Treatment of Cancer Quality of Life Questionnaire-C30 and European Organization for Research and Treatment of Cancer Quality of Life Questionnaire-BR23

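### The primary analysis is a stratified log-rank test with Cox hazard ratios, but the primary outcomes are continuous changes from baseline to 12 weeks, with no event to time

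*Protocol article*

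**What the plan says.** **Analysis.** The Statistical Analysis section states: "The primary analysis will be an intent-to-treat analysis, which will be conducted by using a 2-sided, stratified log-rank test". For the size of the effect it says: "Cox proportional hazard regression models will be used to estimate hazard ratios with 95% CIs to quantify the effect of the intervention", and this is done "after adjusting for stratification, age, and BMI". The only other inferential method named there is Pearson correlation, which measures association and does not compare the arms.

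**Outcomes.** The Methods paragraph of the abstract says: "The primary outcomes will include changes in strength, body composition, and physical function in breast cancer survivors". Under Study Objectives, the primary hypothesis is that "creatine supplementation will result in significantly greater gains in strength and physical function and improved body composition" compared with exercise alone.

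**Timing.** Outcome Assessments says: "Assessments will be performed at baseline and at the end of the study". The schedule of events (Table 1) agrees: strength testing, dual x-ray absorptiometry and the 6-minute walk appear only at the baseline visits and the 12-week visits.

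**Randomization.** Allocation describes 1:1 assignment and says: "We will use randomized blocks to conceal the group allocation results from the patients, recruitment staff, and assessment staff". It names no stratification factor.

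**The concern.** Log-rank tests and Cox models compare how soon something happens. They need an event, a time origin, an observed or censored time for each participant, and, for the stratified version, named strata. The primary question here is how much strength, function and body composition change, and each quantity is seen once after baseline.

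If the text is followed, the trial has no primary analysis that can be carried out. Whoever runs it must choose something else, possibly after seeing the data, and the protocol neither fixes nor limits that choice. The effect measure is also of little use for the trial's declared purpose of supplying parameters for later studies: planning a trial with continuous outcomes needs a between-group mean difference and an SD, and a hazard ratio gives neither.

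**Working it through.** **1. Does the plan supply what the test needs?**

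| Needed by log-rank/Cox | In the protocol article |
|---|---|
| Event | None defined for any primary outcome |
| Event time | One post-baseline assessment, at 12 weeks |
| Censoring rule | None |
| Strata | Mentioned in Statistical Analysis; none named there or in Allocation |
| Outcome scale | Repetition-maximum load, isometric force, grip strength, absorptiometry masses, walk distance: all continuous |

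Adverse-event onset and withdrawal could be timed, but neither is a primary outcome. The stated hope that creatine will accelerate gains does not help, because the speed of a gain cannot be seen from two measurements.

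**2. What happens if it is run on the 12-week visit?** At a single time with n1 and n2 at risk (n = n1 + n2) and d events in all, d1 of them in arm 1:

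- O − E = d1 − n1·d/n
- V = n1·n2·d·(n − d) / [n²(n − 1)]

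If all 30 participants have an event at week 12: O − E = 15 − 15×30/30 = 0, and V = 15×15×30×0 / (900×29) = 0. The statistic is 0/0. With no events it is also undefined.

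**3. What if an event is invented?** The protocol proposes neither option below, so these figures only illustrate the cost. They assume normal outcomes with equal SDs, two-sided 0.05 and 15 per arm, in 20,000 to 40,000 simulated trials. The true differences are assumptions, because the article gives no effect size or SD.

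| Method | Power at 0.8 SD | Power at 1.06 SD |
|---|---|---|
| t-test | 56% | 80% |
| Log-rank, responder = above pooled median | 31% | 53% |
| Log-rank, responder = above midpoint of the arm means | 38% | 60% |
| Log-rank, outcome value used as the time | 52% | 75% |

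With the planned 12 completers per arm, power at 0.8 SD is 46% (t-test), about 30% (median split) and 38% (midpoint cut).

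Part of the median-split loss is discreteness. With 15 events among 30, V = 15⁴/(900×29) = 1.94. A 10–5 split gives 2.5²/1.94 = 3.22, below the critical value of 3.84, and an 11–4 split gives 3.5²/1.94 = 6.32. The test's true size is therefore 2.7%, not 5%.

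Using the value as the time costs little power, but the resulting hazard ratio is a rate per kilogram or per metre and has no useful meaning.

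**4. What does a suitable analysis offer with the same participants?** The sample size of 30 rests on feasibility precedent, so there is no power figure to reproduce. For a t-test at 80% power, the detectable difference is 1.06 SD with 15 per arm and 1.20 SD with 12.

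Adjusting the 12-week value for its baseline leaves a variance of 1 − ρ² (in units of the outcome variance), where ρ is the baseline-to-follow-up correlation. An analysis of change scores leaves 2(1 − ρ). The ratio is (1 + ρ)/2: 0.75 at an assumed ρ of 0.5 and 0.90 at 0.8.

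With 15 per arm, the detectable difference in SDs of the 12-week value (normal approximation) is 1.02×√(1 − ρ²). This gives 0.89 at ρ = 0.5 and 0.61 at ρ = 0.8.

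**The case against.** No argument was found that rescues the stated test. A separate analysis plan may exist, but the article names the test and the effect measure outright, so a plan with a workable method would contradict it.

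Some points do limit how far the criticism goes:

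- **Strata.** This is a condensed article, and factors may be listed in the full protocol. What can be said is that stratification is invoked and no factor is named here. That stands.
- **Baseline covariate.** The outcomes are already changes, so the baseline is used in some form, and covariates are often left to the analysis plan. Its absence from the adjustment list is a secondary point about precision.
- **Simulated powers.** They belong to analyses that nobody proposed, depend on an arbitrary cut, and partly reflect a conservative test. They are best read as a range.
- **Planning information.** The article also promises descriptive statistics, which could supply group means and SDs whatever test is used. The harm falls on the stated inference and effect measure, not on everything the trial will report.
- **Timing of a change.** The statistician's blinding does not by itself make a late change safe, because the principal investigator and participants are not blinded and nine patients had enrolled by October 2021.

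**Conclusion.** The concern holds and must be fixed. The stated primary test and effect measure do not fit the primary outcomes: they need an event and a time, and the plan measures continuous quantities once after baseline. This conclusion follows from the text and needs no numerical assumption.

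The cost of a workaround does depend on assumptions. With normal outcomes, 15 per arm and a true difference of 0.8 SD, an invented responder definition lowers power from 56% to between 31% and 38%. With 12 per arm the fall is from 46% to between about 30% and 38%. In either case it compares responder proportions, not size of gain. The unnamed strata and the missing baseline covariate are lesser defects in the same sentences.

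**What to change.** Replace the log-rank and Cox sentences in Statistical Analysis with wording such as:

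> Each continuous outcome will be analysed by a linear model (ANCOVA) of the 12-week value on randomized group, adjusting for the baseline value of that outcome, age and BMI, with participants analysed as randomized. The adjusted mean difference and its 95% CI will be reported.

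Delete the references to stratification. If the REDCap list was in fact stratified, name the factors under Allocation and enter them as covariates.

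This model on observed values drops anyone without a 12-week measurement, so it does not alone deliver the intent-to-treat analysis the article promises. The text or the analysis plan should say how such participants are handled.

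The cost is a wording amendment: the baseline and 12-week measurements, age and BMI are already within the trial's data, and the sample size is unchanged. The amendment should be dated, and made before anyone reviews outcome data by arm. If that point has passed, the report should say so.
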